#### Clinical Outcomes

Retention in HIV care and viral suppression are measured using standardized performance measures developed by the HRSA/HIV/AIDS Bureau [89]. Measures selected for this study are retention in HIV medical care (2 or more visits separated by at least 90 days for HIV care within the measurement year) and HIV load suppression (the most recent viral load <200 copies/mL during the measurement year). Values for outcome variables (engagement in care and viral suppression) are derived from a retrospective medical record review conducted by site study staff using a study-specific form. Engagement in care is determined by at least one office visit with an HIV clinician per 6-month interval for 12 months before and 6 months after study enrollment. Viral suppression is determined by assessing the participant’s viral load, as noted in laboratory values, typically required at least every 6 months per the standard of care. A value of <200 copies/mL is considered suppressed. Values for each variable are established for the year before study enrollment, at baseline enrollment, and then at 6-month intervals for 18 months.

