### Power Analysis

Group sample sizes of 106 in the Positive Peer group and 106 in the control group achieve 90% power to detect a difference between group proportions of 0.20. This is the minimum sample size required in each group to detect the desired difference in proportions. The proportion in group 1 (the treatment group) is assumed to be 0.60 under the null hypothesis and 0.80 under the alternative hypothesis. The proportion in group 2 (the control group) is 0.60. The test statistic used is the 2-sided *Z* test with pooled variance. The significance level of the test was set at .05. Several assumptions regarding baseline viral suppression were tested based on the literature. The current sample size is based on 63% viral suppression at baseline and a planned 80% in the intervention group. If baseline viral suppression is lower, a smaller sample size would be needed to demonstrate a 20% improvement in viral suppression. Based on this estimation, we aim to recruit and randomize 250 eligible individuals to the study from 6 clinic sites over 24 months, allowing for potential loss to follow-up. It is important to note that patients without documentation of a clinic visit during the assessment period are designated as out of care and will be assumed to be HIV virally unsuppressed. Available data on other outcomes and covariates, however, will be handled using mixed-effects models, which employ maximum likelihood estimation and assume missing-at-random patterns to support valid inferences.

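### The unsuppressed assumption is triggered by a missing clinic visit rather than a missing viral load, and the loss allowance in the sample size does not fit a rule that keeps losses as failures

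*Protocol article*

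**What the plan says.** Three statements in the protocol article's Power Analysis section bear on this point.

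- **Failure rule.** Those lacking any recorded "clinic visit during the assessment period are designated as out of care and will be assumed to be HIV virally unsuppressed".
- **Recruitment target.** The trial will "recruit and randomize 250 eligible individuals to the study from 6 clinic sites over 24 months, allowing for potential loss to follow-up". No loss rate is given, and the section does not say whether the assumed 60% and 80% already count lost patients as unsuppressed.
- **Everything else.** "Available data on other outcomes and covariates, however, will be handled using mixed-effects models, which employ maximum likelihood estimation and assume missing-at-random patterns".

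The outcome is defined elsewhere. Clinical Outcomes bases suppression on the participant's "viral load, as noted in laboratory values, typically required at least every 6 months per the standard of care", with values below 200 copies/mL counted as suppressed. Planned Statistical Analysis defines it as the proportion of enrolled patients whose 6-month viral load is below 200 copies/mL. That section also defines retention by laboratory results in each 6-month period, whereas Clinical Outcomes defines engagement by office visits.

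**The concern.** The failure rule depends on a different variable from the one that defines the outcome. A patient with a suppressed laboratory value in the window but no documented visit is suppressed under the two outcome definitions and unsuppressed under the rule. Planned Statistical Analysis counts that patient as contributing to retention for the period, while Power Analysis calls the same patient out of care. So the article itself treats laboratory results and visits as separable.

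Visits are also something the app is meant to change: Study Rationale and Objectives expects it to normalize and reward care visits. If a missing visit alone makes a patient a failure, a difference between arms in visits feeds into the suppression comparison even where viral loads do not differ.

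The sample size has a related problem. Dividing a required number by one minus the loss rate replaces patients who drop out of the analysis. Under the failure rule nobody drops out of the suppression analysis. If the assumed rates describe followed patients only, losses lower both proportions and, when equal across arms, narrow the difference. If the rates already include losses, no inflation is needed for this outcome.

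**Working it through.** **Inputs (Power Analysis):** control 0.60, app 0.80; "The test statistic used is the 2-sided" Z "test with pooled variance"; "The significance level of the test was set at .05"; 106 per group, said to "achieve 90% power to detect a difference between group proportions of 0.20"; 250 to be randomized, hence 125 per arm at 1:1. The section also cites 63% at baseline; the 0.60 used here is the figure paired with the stated difference of 0.20.

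**Formula.** With d = p2 − p1 and p̄ = (p1 + p2)/2,

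power = Φ{ [d − 1.96·√(2p̄(1 − p̄)/n)] / √([p1(1 − p1) + p2(1 − p2)]/n) }.

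**Step 1: the plan's own figure.** For 0.60 vs 0.80 and 90% power, the pooled formula gives 109 per group. The unpooled one gives (0.24 + 0.16)(1.96 + 1.2816)²/0.04 = 105.1, so 106. Pooled power at 106 is 89.4%. The stated size reproduces.

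**Step 2: implied loss.** 1 − 212/250 = 38/250 = 15.2%. This is inferred; the article does not state it.

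**Step 3: rates already include losses as failures.** 0.60 vs 0.80 at 125 per arm gives power 93.7%.

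**Step 4: rates apply to followed patients only.** Assume loss L is equal in both arms and scored as failure, so each rate is multiplied by (1 − L), with 125 per arm analysed.

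| Loss | Control | App | Difference | Power | Per arm for 90% |
|---|---|---|---|---|---|
| 5% | 0.570 | 0.760 | 0.190 | 89.4% | 128 |
| 10% | 0.540 | 0.720 | 0.180 | 84.3% | 150 |
| 15.2% | 0.509 | 0.678 | 0.170 | 78.3% | 175 |
| 20% | 0.480 | 0.640 | 0.160 | 72.4% | 201 |

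For the 15.2% row: p̄ = 0.5936; the null standard error is 0.06213 and the alternative 0.06119; (0.1696 − 1.96 × 0.06213)/0.06119 = 0.78, and Φ(0.78) = 0.78. Had the 15.2% left the denominator instead, 106 per arm would remain and power would be 89.4%.

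**Step 5: unequal loss, averaging 15%.** With 18% control and 12% app: 0.60 × 0.82 = 0.492 vs 0.80 × 0.88 = 0.704, difference 0.212, power 93%. Reversed: 0.60 × 0.88 = 0.528 vs 0.80 × 0.82 = 0.656, difference 0.128, power 54%.

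**Step 6: the visit trigger, illustrated with assumed rates.** Suppose 70% in each arm have a suppressed value whether or not they had a visit, and visits are documented for 85% of controls and 95% of app users. The literal rule gives 0.70 × 0.85 = 0.595 vs 0.70 × 0.95 = 0.665. That is 7 points produced by visits alone, with about a 21% chance of significance at 125 per arm. It is an upper-end illustration, because it lets patients without a visit have laboratory values as often as the rest. The article gives no figure for how many would.

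**The case against.** **The rule may only fill gaps.** An assumption naturally replaces an unknown value, and nothing in Power Analysis says an observed viral load is discarded. A reader might infer that the rule certainly overrides laboratory data and yields wrong results. The text does not establish that; it establishes a trigger that conflicts with the outcome definitions if followed as written. Scoring missing outcomes as failures among all enrolled is itself an accepted convention. Some overlap with retention remains under any such rule, including the one proposed below. What stands is that the trigger should be the missing quantity.

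**A visit without a viral load is not uncovered.** One might think such a patient falls between the rules. Planned Statistical Analysis uses all enrolled patients as denominator and requires a measurement below 200 copies/mL for the numerator, so that patient already counts as not suppressed.

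**Power.** It is tempting to conclude that the stated 90% holds on no reading, or that the trial is underpowered. Neither follows. The article attaches 90% to 106 per group and states neither a power for 250 nor a loss rate. One reading exceeds 90%; the other reaches 78% only at an inferred loss taken as equal across arms. The app is expected to improve retention, so lower loss in that arm could raise power. The extra patients also serve the questionnaire outcomes, where losses are truly missing. The inconsistency between inflation and rule remains.

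**Covariates.** The sentence refers to available data and does not promise to recover missing covariates. Baseline covariates are completed in person at enrollment. Several time-varying constructs are also outcomes, for which the likelihood approach is right, and mediation models may treat mediators as endogenous. This supports only a wording correction for the Aim 2 models, not a claim that participants will be dropped.

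**Sensitivity analyses.** Imputation and tipping-point details are commonly left to an analysis plan that is not shown here, so their absence is no defect.

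**Conclusion.** The point holds in limited form. The article defines suppression by viral load and assigns failure by absence of a visit; these disagree for a patient with a suppressed value and no documented visit, and the visit trigger exposes the comparison to an effect of the app on attendance. The size of that exposure cannot be determined from the article; the 7-point illustration rests wholly on assumed rates.

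The loss allowance and the failure rule also treat lost patients differently. At 125 per arm, power is 93.7% if the 60% and 80% rates already count losses as failures. Otherwise it ranges from 89.4% to 72.4% for equal losses of 5% to 20%, with 78.3% at the implied 15.2%. Unequal loss could put it on either side of these figures. This concerns the stated basis for power, not the validity of the eventual result.

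The covariate wording is a minor, secondary matter: maximum likelihood handles missing outcomes under missing at random, but a standard mixed-model fit drops records with missing time-varying covariates.

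**What to change.** 1. Derive suppression from any viral load in the assessment window, whether or not a visit is recorded, and apply the unsuppressed assumption only when no viral load exists.
2. State whether the 60% and 80% rates already count lost patients as failures, give the assumed loss rate by arm, and restate power at 125 per arm accordingly. If losses are already counted, say that the increase to 250 serves the questionnaire outcomes.
3. Limit the mixed-model sentence to missing outcomes, and leave the handling of missing time-varying covariates to the analysis plan.

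The cost is small: revised wording, one changed derivation rule and a short power statement. Viral loads and visit dates are already abstracted from medical records, so no new data collection is needed. Accrual is planned to run until November 2026, and the rule should be settled before outcome data are examined by arm.

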### Planned Statistical Analysis

Aims 1 and 2 entail data collection and analysis to provide evidence of PPA effectiveness. Outcomes include retention in HIV care (proportion of enrolled patients with laboratory results in each 6-month period of the study), HIV load suppression (proportion of enrolled patients whose viral load measurement at 6 months in the study is <200 copies/mL), as well as self-reported psychosocial variables, specifically perceived technology affordances, attitudes toward technology, and self-efficacy for managing chronic conditions. We expect that key demographics, technology covariates, and PPA use will predict self-efficacy, which will be directly associated with (1) retention in care, (2) viral suppression, and (3) HIV-related perceived stigma. Additionally, we plan to test potential covariate mediation and examine theoretical linkages in our model of PPA effects.

Analyses of repeated measures will be performed using generalized linear mixed-effects models with a logit link function for binary outcomes (ie, viral suppression and engagement in care) and linear mixed-effects models for continuous outcomes (eg, perceived stigma, resilience). Time will be treated as a fixed, repeated factor within patients, and patient-specific random effects will be included to account for within-patient correlation. To appropriately model the hierarchical structure of observations nested within patients and patients nested within sites, the site will be included as a random effect, providing an estimate of between-site variability. Multilevel mediation models will be used to evaluate potential mediating effects of covariates. *P* values will be adjusted using Bonferroni or Benjamini-Hochberg correction procedures to control the family-wise type I error rate due to multiple comparisons across distinct psychological outcomes.

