## Abstract

**Background:**

People at greatest risk for poor HIV outcomes include young (13-34) people of color who have sex with men. Individuals in this population are least likely to be aware of their HIV status and are at the highest risk for disengaging from medical care and antiretroviral therapy. The Positive Peers mobile app (PPA) was designed to engage this population with real-time social support, HIV and healthy lifestyle information, and medical management tools. We expect that greater PPA engagement will predict key HIV care outcomes. Study predictions are grounded in a user-centric model of digital media use and the perceived affordances of the PPA.

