### Study Rationale and Objectives

We expect the PPA to support engagement in HIV care by normalizing and rewarding care visits, promoting health literacy, reducing stigma, and enhancing inclusion, thereby allowing users to help others with similar challenges. Our goal is to increase HIV viral suppression rates by at least 15% by offering practical and peer support through a smartphone app. Specific aims addressed by the protocol described in this manuscript are (1) comparing the effectiveness of HIV care supported by the PPA with usual care for improving retention in HIV care and viral suppression among high-priority adolescents and young adults with HIV; (2) identifying factors that predict user engagement with primary PPA components and associated effects on retention in care, viral suppression, and HIV-related perceived stigma; and (3) evaluating PoPIT implementation across sites and over time. Figure 1 illustrates the conceptual model of the PoPIT study’s influence and outcomes. This paper describes the protocol used to achieve these aims in a randomized clinical trial with a concurrent qualitative evaluation focused on user experience.

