### Intervention

As described above and elsewhere, PPA is a password-protected, multifunction mobile app for supporting retention in HIV care and viral suppression [17]. Before clinical trial use, the color scheme and fonts were refreshed, the digital architecture of the app was evaluated and debugged to ensure reliability, and accessibility was upgraded to comply with Web Content Accessibility Guidelines (WCAG) 2.1 Level AA and Section 508 standards. All original app functions—that is, the article feed, first-person narratives, customizable reminders, local resources, community forum, and private chat function—remain organized as they were in the pilot study. A Positive Peers brand guide was created in the initial design phase by a professional marketing team to preserve PPA’s visual and content design. Informative articles are written by agency copywriters and study staff and are then vetted by clinicians. Participants are not directed or required to use the app in any specific way.

PPA is continuously monitored by a dedicated digital design team and PoPIT study staff. Conferences are held regularly to address issues identified by app administrators, reported by users, or noted by other study staff. The study coordinator relies on an electronic reporting system to alert the technical team, who respond promptly and effectively to app issues or bugs. PPA provides instructions for use, community standards, a privacy policy, and accessibility standards in an “About” tab within the app. All participants are made aware of data collection practices during informed consent. PPA does not sell or display advertising or rely on commercial sponsorships at this stage of development.

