### Ecological Momentary Assessments

EMA is a method widely used to study behavior and mood in the settings in which they naturally occur [74,75]. Because of this immediacy, EMAs can support ecological validity by mitigating the memory limitations inherent in retrospective self-reports. Four general characteristics define EMAs: (1) data collection in real-world environments, (2) a focus on the individual’s current state of mind, (3) strategic selection of assessment moments, and (4) repeated assessments over time. Although the PPA records and maintains a log of each user action within the app, it remains unclear how users perceive the app while actively using it.

The PPA is premised on a user-centered model of digital media effects [59,61,63]. This approach suggests that users’ needs and the characteristics of the technology (ie, its affordances) interact to shape user engagement. Greater engagement with the mobile app is expected to influence self-efficacy in HIV management and increase the likelihood of favorable HIV clinical outcomes. As EMAs occur repeatedly in real time, they provide an opportunity to assess user engagement with the PPA more immediately than retrospective self-report. The goal of the EMA methodology is to link tracked physical interactions with the app (ie, natively recorded usage data) to users’ immediate perceptions of engagement in real time.

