### Measures

#### Selection of Standardized and Validated Study Measures

Selected study measures make use of the PhenX toolkit [78], Patient-Reported Outcomes Measurement Information System (PROMIS) Toolbox [79,80], and Health Resources and Services Administration (HRSA) HIV/AIDS Bureau reporting standards [81]. Measures were selected based on our preliminary work, theoretical model, and relevance to the population (Table 3). The PhenX Toolkit is a searchable online database of recommended measurement protocols for human studies [82]. Database protocols are well established, broadly validated, reliable, and low burden for study participants. Measures for this study, derived from the PhenX toolkit, include a set of demographic characteristics and social determinants of health, as well as the Medical Outcomes Study Social Support Survey.

**Table 3 table3:** PoPIT^a^ constructs, measures, and prospective data collection.

Construct	Measure	Collection
Participant characteristics [82]	PhenX: age, ethnicity and race, biological sex, sexual orientation, sexual identity, marital status, and educational attainment	Baseline^b^
Social determinants of health [83]	AAFP^c^ Social Needs Screening Tool: housing, food and transportation insecurity, utilities, employment, finances, and personal safety PhenX: internet access, access to health technology, and general social media use	Baseline and 12 months
Attitudes toward technology [84]	Social Media Usage & Attitudes Scale (MTUAS^d^)	Baseline, 6, and 12 months
Technology affordances [85]	Mobile Application Affordances Measure	3 and 6 months after app initiation
PPA^e^ engagement	Number of logins, duration (minutes), number of sessions, and engagement counts for each PPA function (articles, med tracker, resources, forum, and chat)	Concurrent with participant app use
Self-efficacy for managing chronic illness [86]	PROMIS^f^ subscales: managing emotions, social interactions, medication adherence, and general self-efficacy	Baseline, 3, 6, 9, and 12 months
Social support [87]	Medical Outcomes Study Subscales: emotional/informational support, tangible/instrumental support, and positive social interaction	Baseline, 3, 6, 9, and 12 months
Perceived HIV stigma [88]	HIV Stigma Scale subscales: personalized, disclosure, negative self-image, and public attitudes	Baseline, 3, 6, 9, and 12 months
Engagement in HIV care [89]	Pre- and postclinic visit dates and count	12 months before enrollment and 18 months after study completion

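### Aim 2, which rests partly on self-chosen app engagement, is labelled effectiveness evidence alongside the randomised Aim 1, though it can support only an association

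*Protocol article*

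**What the plan says.** All references are to the protocol article.

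- **Planned Statistical Analysis** opens with "Aims 1 and 2 entail data collection and analysis to provide evidence of PPA effectiveness". It then states the expected path: "We expect that key demographics, technology covariates, and PPA use will predict self-efficacy, which will be directly associated with" retention, suppression and stigma. Mixed models are specified, and "patient-specific random effects will be included to account for within-patient correlation". Multilevel mediation models are also planned.
- **Study Rationale and Objectives** defines Aim 2 as "identifying factors that predict user engagement with primary PPA components and associated effects on retention in care, viral suppression, and HIV-related perceived stigma".
- **Abstract, Background**: "We expect that greater PPA engagement will predict key HIV care outcomes".
- **Ecological Momentary Assessments** uses causal language: "Greater engagement with the mobile app is expected to influence self-efficacy in HIV management and increase the likelihood of favorable HIV clinical outcomes".
- **Intervention**: "Participants are not directed or required to use the app in any specific way".
- **Table 3** measures engagement by logins, minutes, sessions and "engagement counts for each PPA function (articles, med tracker, resources, forum, and chat").
- **Power Analysis** assumes that a patient with no documented clinic visit in the assessment period is unsuppressed.
- **Study Design** makes the randomised 6-month comparison the estimate of what the app adds beyond the effects of trial participation.

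**The concern.** Randomisation decides who gets the app and when. It does not decide how much anyone uses it. A comparison of heavier with lighter users is therefore observational, even inside a randomised trial, and the document gives it the same label as the randomised contrast.

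Three features make a favourable association without any app effect plausible:

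- A person disposed to take treatment and attend visits may also be disposed to open a health-management app.
- One engagement component, the medication tracker, is itself close to adherence behaviour.
- Someone who leaves care is scored unsuppressed. If such people also stop using the app, the scoring rule helps to create the link.

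The patient random effects do not solve this. They are stated as handling within-patient correlation, and they assume that patient-level differences are independent of the exposure. The path from app use through self-efficacy to outcomes has the same weakness.

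At stake is the reading of the results. If the randomised contrast were null or equivocal and the engagement coefficient positive, the stated wording would allow the second to be presented as evidence that the app is effective.

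**Working it through.** **The plan's own figure.** The document gives no figure for the engagement analysis. Its only related calculation is for the randomised comparison: 0.60 versus 0.80, two-sided 0.05, 90% power, 106 per arm.

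- Unpooled formula: (1.960 + 1.282)² × (0.60×0.40 + 0.80×0.20) / 0.20² = 105.1, so 106 per arm.
- Pooled formula: 108.2, so 109 per arm. Power at 106 per arm is 89.4%.

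The figure reproduces to within rounding and choice of formula, and this point does not affect it.

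**Check 1: the gap that an inert app could show.** No input on confounding is in the document, so all are assumed and varied. Let T be a standard normal trait.

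- P(high engagement | T) = expit(bT)
- P(suppressed | T) = expit(logit(p) + bT), where p is suppression at the average trait value
- There is no path from engagement to suppression.

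The gap is P(suppressed | high) − P(suppressed | low), obtained by integrating over T.

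| p (assumed) | b per SD (assumed) | High users | Low users | Gap, points |
|---|---|---|---|---|
| 0.70 | 0.3 | 70.6% | 68.7% | 1.8 |
| 0.70 | 0.5 | 71.4% | 66.6% | 4.8 |
| 0.70 | 1.0 | 74.7% | 59.1% | 15.5 |
| 0.60 (plan's control rate) | 0.3 | 60.8% | 58.8% | 2.1 |
| 0.60 | 0.5 | 62.2% | 56.8% | 5.4 |
| 0.60 | 1.0 | 66.8% | 49.9% | 16.9 |

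**Check 2: does one baseline indicator remove the gap?** Add a binary prior-suppression indicator that depends on T with the same b, then average the gap over its two strata. At p = 0.70 the gap falls from 15.5 to about 13.3 points for b = 1.0, and from 4.8 to about 4.6 for b = 0.5. Adjustment helps only a little, because one yes/no value is a coarse proxy for the trait.

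**Check 3: how often would the test favour an inert app?** This uses a separate simulation with 2,000 runs per setting. Suppression is 60% overall, the trait effect on suppression is 1.0 or 1.5 log-odds per SD, and engagement correlates with the trait at rho. Suppression is regressed on engagement among 125 app users (250 randomised ÷ 2) or 250. The nominal rate of a significant result in favour of the app is 2.5%.

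| rho (assumed) | 125 users | 250 users |
|---|---|---|
| 0 | 1.6–1.8% | 2.6–2.8% |
| 0.1 | 6–7% | 9–13% |
| 0.2 | 14–20% | 25–38% |
| 0.3 | 26–43% | 47–71% |
| 0.5 | 63–85% | 91–99% |

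With 125 users and rho 0.3, adding a prior-suppression indicator (40% overall, assumed) leaves 20–27%. In the same runs the randomised two-proportion test rejects in 4–6% two-sided, as it should.

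**The case against.** The strongest reply is that the document already says where proof of an app effect comes from. Study Design makes the randomised 6-month comparison the estimate of benefit. The aims use the word effectiveness only for Aim 1, and the path in the analysis section is worded as prediction and association. On this view the opening sentence is a loose introduction to two aims. That stands as far as the primary comparison goes, but the opening sentence still names both aims, and nothing labels the engagement results as associational.

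Three stronger readings are tempting, and the documents do not support them:

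- **The trial as a whole could declare an inert app effective.** Not through the primary comparison, which is protected by randomisation. The risk is confined to the engagement and mediation results.
- **Engagement and outcome have no time order.** The data are ordered. PPA Engagement describes real-time logging with monthly reports, and Clinical Outcomes sets values for the prior year, baseline and each 6 months to 18 months. Only the exposure window is unstated, and that may be fixed in an analysis plan not shown.
- **Prior-year suppression and visits are collected but will not be used.** Nothing says so. The sentence naming demographics, technology covariates and app use states an expectation about self-efficacy. It is not a closed adjustment list.

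The direction of the bias is also open. The Social Networking Theory and Social Support section says that recently diagnosed people lean more on online support and that stressors can drive support seeking online. If needier patients use the app more, the association could hide a benefit. This objection stands, but it too argues against counting the association as evidence of effectiveness.

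**Conclusion.** The point holds in limited form. The document gives a non-randomised association the same label as the randomised contrast and describes it causally in one place. That label is stated text, so an unseen analysis plan that added covariates or lags would not correct it.

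The 6-month randomised comparison and its sample size are unaffected. For Aim 2, an inert app could show a gap of about 2, 5 or 16 points at an assumed trait strength of 0.3, 0.5 or 1.0 log-odds per SD, with 70% suppression at the average trait value. Only the strongest of these is of the order of the 15% improvement goal in Study Rationale and Objectives. With no correlation between trait and engagement there is no excess of false positives. Confounding by adherence is therefore plausible but not shown, and neither its size nor its sign can be read from the document.

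**What to change.** **Essential.** Change the opening of Planned Statistical Analysis to say that evidence of effectiveness rests on the randomised Aim 1 contrast alone, and that Aim 2 engagement and mediation results are reported as associations among app users. Bring the causal sentence under Ecological Momentary Assessments into line.

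**Supporting.** In the Aim 2 models:

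- Count engagement in a window that closes before the outcome window opens, for example the first 3 months of app access. Other windows are defensible; the need is to fix one in advance.
- Adjust for pre-enrolment suppression, prior-year visits, entry category (newly diagnosed, out of care, not suppressed), age stratum and site.
- State that adjustment reduces confounding and does not remove it.

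**Cost.** The wording change costs nothing but a more cautious claim. The modelling is modest and needs no new data, since the outcome histories, monthly engagement reports and eligibility information already exist. Engagement after the chosen window drops out of that particular model. Accrual runs to November 2026, so there is time to make the change before the analysis.
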